| Protocol | | 1.0 / 201105016 | | | | | | | | |
| Informed consent form | | 1.0 / 201105016 | | | | | | | | |
| Case report form | | N/A | | | | | | | | |
| Investigational brochure | | N/A | | | | | | | | |
| Advertisement | | N/A | | | | | | | | |
| (add or delete column when necessary) | |  | | | | | | | | |
| Study period | | __1_ year_0__month | | | | | | | | |
| Apply status | | ■ Expedited review | | | | - Full board review | | | | |
| - This protocol is similar to other protocol approved by IRB, IRB No.： - For other IRB review   ■ No  □ Yes  □with review results, please attach： 。  □Other IRB has approved, please attach approval letter。 | | | | | | | | |
| Executing institute  (Location) | | - CCH - CCH branch： - other domestic institute： - other participating country：   ■ Other：Four companies. The companies having good research cooperation with the PI will be chosen.  If the protocol led by CCH principal investigator, does it need to set up multi-center communication channel?  □Yes ■No □Do not apply | | | | | | | | |
| Research type | | - Drug registration (Please attach investigational medicinal product/ vaccine introduction) - Drug academic research (Please attach investigational medicinal product/vaccine introduction)) - Post marketing surveillance (Please attach investigational medicinal product/vaccine introduction)) - Medical devices or medical devices with new medical techniques (Please attach medical devices or medical devices with new medical techniques introduction) - Medical techniques (Medical technique introduction) - Generic drug bioavailability, bioequivalence - Genetic research (including genetic test, transgenic, stem cells, genetic recombinant ) - Epidemiological studies - Social behavioral sciences   ■ Other：_Behavior treatment_______ | | | | | | | | |
| Research model | | ■ Intervention research   - 1. Research purpose：   □Treatment  □Prevent  □Diagnose  □Supportive treatment  □Screening  □Health policy  □Basic medical  ■other: Enhancing mental health   - 1. Random distribution：   □Single group  ■random distribution  □non-random distribution   - 1. Blinding test：   ■Open  □single blind  □double blind  □triple blind   - 1. Comparator：   □Placebo  □Dosage comparison  □other effective treatment  □Previous information  □None  ■other waiting-list control group   - 1. Intervention model：   □single group  □double group parallel  □double group intersect  ■more than 3 groups   - 1. End point：   □safety  ■efficacy  □Bioequivalence  □Bioavailability  □Pharmacokinetics  □Pharmacodynamic   - Observative research  1. Observation model：   □Cohort Study  □Case control study  □Case study  □case crossover study  □ecological or social research  □family research  □other   1. data collection period：   □Retrospective  □Prospective  □cross-sectional study | | | | | | | | |
| Measure tools | | ■ Questionnaire  □Record (including interview, recording, video tape recording) | | | | | | | | |
| Retention of biological samples | | - Non DNA biological samples (e.g. fix structure, serum…) - Retain DNA biological samples (e.g. frozen structure…)   ■ No biological samples/none retain biological samples | | | | | | | | |
| Test phase | | - phase I：The safety research in understanding the toxicity of the drug with healthy volunteer subjects. The subjects are healthy volunteers. - phase II：The initial efficacy observation in understanding the efficacy of the drug. The subjects are patients. - phase III： The complete efficacy evaluation in order to confirm the efficacy and the safety. The subjects are patients and comparator groups. - Phase IIIa：Haven’t passed the review of the competent authority. - Phase IIIb： Passed the review of the competent authority. - phase IV：post marketing surveillance (PMS) to see if there is any adverse reaction for long-term tracking. - Other： 。 | | | | | | | | |
| Sample quantity | | - Global _______ - Domestic _400__ | | | | - CCH：_______ - Other：___(please specify the institute and the number of people) | | | | |
| Trial subjects | | - Age：___18_____～___65_____(years old) | | | | | | | | |
| ■ Normal   - Patient   ■ Male  ■ Female   - Other：______ | | | □Vulnerable groups  □Prinsoner  □Pregnant women  □Infants  □Children  □Disabled people  □Other：________ | | | | | |
| Special condition | | - Intense care - Child intense care - Genetic treatment - Prosthetics | | | - Quarantine - Intravenous injection - Controlled drug - Other：________ | | | | - Surgery - CT - Gynecological supplies | |
| Inclusion criteria | | - 18 Years to 65 Years healthy employees with psychological distress and job strain - Full-time paid workers | | | | | | | | |
| Exclusion criteria | | - Age < 18y or > 65y - Part-time workers - The workers are not willing to take part in the study | | | | | | | | |
| Expected adverse event/serious adverse event | | None | | | | | | | | |
| The management of expected adverse event/ serious adverse event | | None | | | | | | | | |
| Recruit subjects | | - Media advertisement（attach the content） - TV - Radio - Newspaper - Internet - Bill board - Poster - Flyers | | | | | ■ Oral introduction   - Other________ | | | |
| Result report or publication | | Publication in academic journals or presentation in conference. | | | | | | | | |
| 1. Is there special protection in getting the informed consent of the vulnerable groups?   □Yes, specify______  □No  ■NA | | | | | | | | | | |
| 1. Is there Data safety monitoring plan, DSMP?   Explanation: except for minimal risk trials, the protocol should have DSMP. The definition of minimal risk: it means the changes or degrees of hazards caused to the body or mind is equivalent to those caused from the daily life of health subjects, conventional medicine, and psychological examination. The hazard does not increase as participating in the human trial.  □ Yes, attach DSMP protocol  ■ No | | | | | | | | | | |
| 1. Is there Data safety monitoring board, DSMB?   □Yes, attach DSMB protocol  □Comparator research: the main or secondary endpoint of the research is death and/or serious diseases.  □Randomly comparator research: the main research purpose is to evaluate the effectiveness and safety of a new intervene measure of lowering the incident rate of the serious disease or death.  □The early research of high risk intervene measures: whether random or not, e.g. unpreventable, potential lethal complications or common, concerned, preventable adverse event.  □The early phase of innovative intervene measures: the clinical safety information is limited or the previous information leads to potential serious adverse consequences.  □Complicated research or the expected accumulated data is hard to explain, or the accumulated data might affect the research design and the subject safety, especially long term research.  □The data obtained from the research proves to terminate the research. For example, the purpose of an intervene measures is to lower the incident rate or death rate of a serious disease; however, in fact it has adverse response or lack of efficacy that leads to increasing the incident rate or death rate.  □The research conducted under emergency.  □The research involving vulnerable groups.  The frequency of submitting DSMB report：_______________  ■No | | | | | | | | | | |
| 1. Whether to stop or suspend the standard treatment for trial purpose?   □Yes, specify____  □No  ■NA | | | | | | | | | | |
| 1. Whether to include subjects who cannot perform consent?   □Yes, reason______  ■No  □NA | | | | | | | | | | |
| 1. Provide medical care to the subjects during and after the trial?   □Yes  □No  ■NA | | | | | | | | | | |
| 1. Provide the subjects with trial product after the end of study?   □Yes  □No  ■NA | | | | | | | | | | |
| 1. The personnel who might get in touch with the personal information of the subjects (including the medical record and the specimen)?   Include： Principal investigator, coordinate investigator and researchers | | | | | | | | | | |
| 1. The way to keep subject information in confidentiality    - - - Subject identity code    Use English name initials  ■ Code the research information  ■ Lock/encrypt all information   Other： | | | | | | | | | | |
| 1. Whether the research material that does not de-link provides for specific research abroad?   □Yes, attach the warranty that the abroad research institute assure to abide by our national regulations and research material usage scope.  ■No  (Note: research material is the human specimen, nature person information, and other related data, information of the subjects.) | | | | | | | | | | |
| 1. The related procedure of obtaining informed consent:   Apply for waiver or alteration of informed consent? □No ■Yes (Please attach waive or alter informed consent checklist.)   - 1. Who explains to the subject or the legal representative about the research and obtains the consent?   □Principal investigator (including coordinate investigator)  ■Researcher  □Other doctor/research nurse (non coordinate investigator)   - 1. The language used to obtain the informed consent:   □Chinese □Taiwanese ■Chinese+ Taiwanese □Other：   - 1. Expected language understood by the subject or the legal representative   □Chinese □Taiwanese ■Chinese+ Taiwanese □Other：   - 1. The timing of obtaining the informed consent?   □Before screening  □After screening, before randomly assign  ■After screening, after randomly assign  The place of explaining the trial content? The worksites where the participant work for ；How long does it take? About 15-20 minutes | | | | | | | | | | |
| 1. Subject risk and benefit evaluation ：    1. Experiment group：   ■ Equivalent to minimal risk. (Category 1 type risk)   - Greater than minimal risk but has direct benefit to the subjects. (Category 2 type risk) - Greater than minimal risk but has no direct benefit to the subject; however, it helps understand the condition of the subjects. (Category 3 type risk) - Greater than minimal risk but has no direct benefit to the subjects; however, the research can have valuable results. (Category 4 type risk)   1. Comparator：■Yes □No(The following are optional)   ■ Equivalent to minimal risk. (Category 1 type risk)   - Greater than minimal risk but has direct benefit to the subjects. (Category 2 type risk) - Greater than minimal risk but has no direct benefit to the subject; however, it helps understand the condition of the subjects. (Category 3 type risk) - Greater than minimal risk but has no direct benefit to the subjects; however, the research can have valuable results. (Category 4 type risk) | | | | | | | | | | |

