**Method**

Study design and the participant

The study will adopt a randomized controlled study design. Four manufacturing factories are chosen for this study. All the full-time workers in the factories will be requested to fill out a questionnaire regarding mental health and job content. The screening procedure was approved by the Institutional Review Board of the Changhua Christian Hospital. After pre-interventions assessment, the workers with psychological distress and job strain would be invited to participant in the study. The workers who are willing to take part in the study will need to give their informed consent and will be the participants for the study. The participants from two of four companies would be allocated into the MBI group (Group M) or the waiting-mindfulness-list control group (Group C-M) by block randomization. The participants from the other two companies will be randomly allocated to Focus group (Group F) or waiting-Focus-list control group (Group C-F). Each group is expected to have about 100 participants. The real number of participants in each group will be depended on how many workers are willing to take part in the study.

Study procedure

After pre-interventions assessment, the workers with psychological distress and job strain would be invited to participant in the study. All the participants will to need to give their written informed content to the research team. The researchers will assign the participants into the intervention groups or control groups by block randomization. After randomization, two well-trained research assistants will notify each participant about the group he or she will take part. The intervention groups will be led by the relevant experts. The contents of the interventions are list below. All the participants would be measured five times with an interval of four weeks between measurements. These measurements will be taken at pre-intervention (T1), at mid-intervention (T2), at the completion of intervention (T3), four weeks after intervention (T4), and eight weeks after intervention (T5). The research assistants will distribute and collect the questionnaire.

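### The IRB form places consent after random assignment and the Method section places it before; the form's order could let refusal depend on arm, so the two must be reconciled

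*Protocol*

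**What the plan says.** The Method section gives the order twice.

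- Under the study design heading: "The workers who are willing to take part in the study will need to give their informed consent". Those who consent are the participants, and the participants are then allocated.
- Under the study procedure heading, the consent sentence, "All the participants will to need to give their written informed content to the research team", comes directly before the allocation sentence, "The researchers will assign the participants into the intervention groups or control groups by block randomization". Disclosure comes last: "After randomization, two well-trained research assistants will notify each participant about the group he or she will take part".

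The IRB application form, which follows the reference list in the same document, has a row on the procedure for obtaining consent. It offers three times: before screening, between screening and assignment, and after both. The third is ticked: "After screening, after randomly assign". The other two are empty.

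Three other entries bear on the consequence. The research-model row of the form ticks open blinding and gives the comparator as "other waiting-list control group". The exclusion criteria on the form include "The workers are not willing to take part in the study", with no time attached. The Method section adds that the number reached in each group will depend on how many workers are willing.

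**The concern.** Consent before allocation ensures that the people compared are the people randomised. A worker who declines at that stage has no arm, so declining cannot differ by arm. If consent is sought after allocation, that protection depends on the worker not knowing the arm when asked.

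In this trial the two offers differ in burden and appeal: a course of group sessions now, or a wait. Nothing is blinded. A worker who declined after assignment could also be read as meeting the unwillingness exclusion, and so be left out of the study instead of being counted as a withdrawal. Refusal could plausibly go with distress, workload or motivation, which are close to what the questionnaires measure. The same reasoning applies to both comparisons, mindfulness against its waiting list and focus group against its waiting list.

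**Working it through.** **The two sequences.** No figure in the plan is in dispute, so the main check is a comparison of texts.

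| Step | Method section | IRB application form |
|---|---|---|
| 1 | Screening questionnaire | Screening |
| 2 | Written consent | Random assignment |
| 3 | Block randomisation | Consent |
| 4 | Group made known | Not placed relative to consent |

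Steps 2 and 3 are reversed. The form had a box matching the Method order and left it empty. Neither text is an amendment log, and no other part of the document settles the order.

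**What follows if the form's order is used.** Let a share p of an arm decline, and let decliners differ from acceptors by d on an outcome, in SD units. The randomised arm mean without any intervention effect is mu = (1 - p) x A + p x (A + d) = A + p x d, where A is the acceptors' mean. So A = mu - p x d. The spurious difference between enrolled arms is

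-(pI x dI - pC x dC),

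where I is the intervention arm and C the waiting list. If d is the same in both arms, this becomes -(pI - pC) x d.

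The documents give none of p or d. The values below are assumptions, chosen only to show the behaviour of the formula.

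- Equal shares and the same kind of decliner in both arms: 0.
- Refusal differing by 10 percentage points, d = 0.5: 0.10 x 0.5 = 0.05 SD.
- Differing by 20 points (30% against 10%), d = 0.5: 0.20 x 0.5 = 0.10 SD.
- Differing by 30 points, d = 0.8: 0.30 x 0.8 = 0.24 SD.

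The sign depends on which arm declines more and on who declines. The documents fix neither.

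**Effect on the planned test.** The figures above concern levels at one time point. The analysis section plans a mixed-design ANOVA over five time points and looks first at the group-by-time interaction. Write d1 for the refuser/acceptor gap at T1 and dt for the gap at a later time. The spurious difference in change from T1 is -(pI - pC) x (dt - d1). With a stable gap of 0.5 and a 20-point difference in refusal, it is 0.10 at T1 and 0.10 later, so 0.10 - 0.10 = 0 in the change. Only selection related to change over time biases the interaction. The simple main effects of intervention that the plan examines next compare levels, so a stable gap would not cancel there.

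**The case against.** The strongest reply is that the Method section is the only narrative of the procedure, is consistent in both its paragraphs, and puts consent first; the tick may be a slip. Even under the ticked order, nothing says that the arm is disclosed before consent is asked. The unwillingness criterion stands beside age and part-time work as ordinary eligibility, and how later decliners are analysed may be left to a statistical analysis plan. All full-time workers complete a mental health and job content questionnaire before invitation, so some baseline information on decliners would exist and selection could be examined and partly adjusted for.

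Most of this stands, and it makes the harm conditional. It does not remove the contradiction. An analysis plan can define an analysis set, but it cannot decide when consent is taken, and staff cannot follow both texts.

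A reader might infer more than the documents support:

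- *That the randomisation is broken.* This requires both the form's order and knowledge of the arm at consent. The form allows the second but does not state it.
- *That the form's request for a waiver or alteration of consent contradicts written consent from participants.* The checklist it refers to is not available, and the request may concern only the factory-wide screening.
- *That one person both assigns and obtains consent.* The role words in the two places are generic and do not show this.
- *That the bias is a known fraction of the treatment effect.* The documents give no effect size and no refusal rate, and a difference in levels does not carry over to the interaction.

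**Conclusion.** The point holds as an internal contradiction on a step that protects the randomised comparison. It should be settled before anyone is allocated. Its consequence is a possibility: arm-dependent refusal can arise only if the form's order is used and workers know or can guess their arm when asked. Under the Method order it does not arise.

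Size and direction cannot be derived from the documents. Under the assumed values shown, with the same gap in both arms, the spurious difference in level at one time point runs from 0 to 0.24 SD in either direction. For the group-by-time interaction it is zero when the gap is stable and refusal differs only in share. The case for correction rests on the contradiction and the low cost of removing it, not on these illustrations.

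**What to change.** 1. On the IRB form, tick the option that places consent between screening and assignment, so that it agrees with the Method section.
2. State beside the exclusion criterion that unwillingness excludes a worker only before randomisation.
3. State that anyone who declines after randomisation stays in the assigned arm and is counted as a withdrawal.

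The cost is an IRB amendment of one tick-box and two sentences, with no extra staff or participants. The downside is that allocation must wait for consent.

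If the sponsor did mean consent to follow assignment, the Method section must change instead. The plan would then have to say how the arm is concealed until consent is given and how randomised decliners are counted and analysed.
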